### Statistical analysis

Statistical analysis will be done using an SPSS software where Percentage, Mean, median and mode will be used for descriptive analysis and for comparing continuous outcomes like ROM, NPRS and SPADI, if the data is normally distributed, a One-Way ANOVA be used to assess differences across the three groups, followed by post-hoc for pairwise comparisons. For non-normal data, the Kruskal–Wallis test is appropriate, followed by Mann–Whitney tests to identify significant pairwise differences. A Kruskal–Wallis H test was conducted to compare the mean ranks of PGIC scores among the SSMP, MWM, and sham groups. TENS exposure will be included as a covariate in the primary outcome analyses.

A sensitivity analysis will be conducted to evaluate the potential influence of TENS on pain (NPRS) and functional (SPADI) outcomes across groups. As this study is designed as a pilot randomized controlled trial, the analysis will primarily focus on estimating preliminary effect sizes and confidence intervals to inform the design and sample size calculation of a future definitive trial.

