**Methods:**

A total of 36 patients with frozen shoulder, will be randomly allocated for 8 weeks into three groups: (a) the SSMP group (n = 12) (b) the mobilization with movement (MWM) group(n = 12) and (c) sham mobilization group (n = 12). Patients with frozen shoulder aged 40–65 and meeting the inclusion criteria will be eligible. Each group will receive 3 sessions in a week for 8 weeks along with different exercises including isometric, eccentric and concentric followed by the functional program. Measurements will occur at four time points: before the initiation of treatment sessions (week 0), followed by 12 treatment sessions (week 4), then 18 treatment sessions (week 6) and two months from the beginning of the trial (week 8). The primary outcome was functional disability (SPADI). Secondary outcomes included pain intensity (NPRS), active shoulder range of motion (ROM), and the Patient Global Impression of Change (PGIC).

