Similarly, MWM is a symptom modification technique designed to reduce pain and restore joint mobility. It has gained widespread clinical utilization due to its demonstrated efficacy in the treatment of adhesive capsulitis. Notably, a systematic review conducted in 2022 concluded that manual therapy interventions, including MWM, are associated with clinically meaningful benefits for patients presenting with shoulder pain and functional limitations [11].

In contrast, sham mobilization is employed in clinical trials as a placebo control to isolate and assess the true efficacy of active manual therapy techniques [12]. The use of such a control is critical for understanding the specific effects of symptom modification approaches and their role in the rehabilitation of musculoskeletal disorders.

Although MWM has shown promising results in clinical trials compared to sham mobilization, the effectiveness of SSMP in reducing pain and disability and in enhancing quality of life for patients with adhesive capsulitis remains an area requiring further investigation. The present trial aims to evaluate the potential benefits of SSMP as a targeted, non-invasive intervention for the management of adhesive capsulitis and to compare its outcomes with those of MWM and sham mobilization.

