## Objective

The primary objective of this study was to evaluate the effectiveness of SSMP compared with Mobilization with Movement (MWM) and sham mobilization in patients with frozen shoulder for improving functional disability, reducing pain, and improving range of motion.

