### Outcome measures

The evaluations will take place at four time points: prior to treatment (week 0), post-treatment (week 4 and 6), and two months subsequent at week 8. The primary outcome of this study was functional disability as measured by the Shoulder Pain and Disability Index (SPADI). In addition, the secondary outcomes included pain intensity measured using the Numeric Pain Rating Scale (NPRS), active shoulder range of motion (ROM), and the Patient Global Impression of Change (PGIC).

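### The primary objective is about SSMP, but SPADI is analysed by a three-group omnibus test followed by unranked pairwise tests, so neither SSMP contrast is singled out

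*Protocol article*

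**What the plan says.** The Objective section reads: "The primary objective of this study was to evaluate the effectiveness of SSMP compared with Mobilization with Movement (MWM) and sham mobilization". The end of the Background has the same focus: "The present trial aims to evaluate the potential benefits of SSMP as a targeted, non-invasive intervention". Outcome measures fixes the endpoint: "The primary outcome of this study was functional disability as measured by the Shoulder Pain and Disability Index (SPADI").

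The Statistical analysis section treats SPADI, NPRS and ROM alike. For normally distributed data, "a One-Way ANOVA be used to assess differences across the three groups, followed by post-hoc for pairwise comparisons". Otherwise a Kruskal–Wallis test is used, "followed by Mann–Whitney tests to identify significant pairwise differences". For PGIC it names only the omnibus step: "A Kruskal–Wallis H test was conducted to compare the mean ranks of PGIC scores among the SSMP, MWM, and sham groups".

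The same section adds that TENS exposure enters the primary outcome analyses as a covariate. It also says that, because this is a pilot, the emphasis is on effect sizes and confidence intervals for designing a definitive trial. No significance level, sidedness or post-hoc method is stated, and no pairwise contrast is named or ranked.

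**The concern.** The objective poses two questions: does SSMP do better than sham, and does it do better than MWM? The omnibus test asks a different one, whether all three arms are equal. The pairwise step then gives MWM versus sham the same standing as the two SSMP contrasts.

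Two things are at stake. First, a significant group difference on SPADI may be due entirely to MWM, and the plan does not say in advance which contrast answers the primary objective. Second, the pilot is meant to supply the effect size for a definitive trial. That calculation needs a target contrast, and an omnibus statistic does not provide one. If the contrast is chosen after the results are seen, the choice can follow the data.

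**Working it through.** **Inputs from the article.** Three arms of 12 (Abstract, Methods; Sample size calculation): 3 × 12 = 36, which matches the stated total. This is a rule of thumb, so there is no power calculation to reproduce.

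**Assumptions, because the article gives none.** Two-sided 0.05; normal data with common SD; effects in SD units; no covariate. Residual df = 36 − 3 = 33; critical values F(2, 33) = 3.285 and t(33) = 2.035. SE of a difference between two arms = √(2/12) = 0.408 SD.

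**Step 1. Omnibus test when only MWM works.** The noncentrality is λ = n Σ(μᵢ − μ̄)². With (SSMP, MWM, sham) = (0, 0.8, 0), μ̄ = 0.267 and λ = 12 × (0.0711 + 0.2844 + 0.0711) = 5.12. The chance of a significant F test is about 48%, and simulation gives 47.7%. For an MWM effect of 0.5 SD it is about 21%, and for 1.0 SD about 68%.

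**Step 2. The pairwise results in those significant trials (MWM effect 0.8 SD, simulated).**

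| Among trials with a significant omnibus test | Unadjusted | Tukey |
|---|---|---|
| MWM–sham significant, SSMP–sham not | 77% | 65% |
| MWM–sham significant, neither SSMP contrast significant | 14% | 27% |

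The second row is smaller because MWM then differs from SSMP as well as from sham. SSMP–MWM is significant after the gate in 39.2% of all trials, and 0.392 / 0.477 = 82% of those with a significant omnibus test (unadjusted).

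**Step 3. Cost of the gate to SSMP versus sham.** Assume effects of 0.8 SD (SSMP) and 0.4 SD (MWM).
- Direct contrast: noncentrality 0.8 / 0.408 = 1.96, power about 48%.
- Omnibus test: λ = 12 × (0.4² + 0² + 0.4²) = 3.84, power about 37%. A gated contrast cannot exceed this.
- Both significant: about 35% (simulated).

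With effects of 1.0 and 0.5 SD, power is about 66% direct and 53% gated.

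**Step 4. Error rate without the gate.** With all arms equal, at least one of three unadjusted pairwise tests is significant in about 12% of trials (11.9% for t tests, 11.4% for Mann–Whitney). With the gate it is about 5% (4.9% simulated).

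**Step 5. Precision.** The 95% CI half-width for one contrast is 2.035 × 0.408 = 0.83 SD. Estimates this imprecise will differ noticeably by chance, which favours naming the contrast beforehand.

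**The case against.** The strongest reply is that this is a pilot sized by rule of thumb, with no pass/fail rule and a stated emphasis on estimates and confidence intervals. Power and significance rates then matter less, and part of the remedy is already promised. The choice of post-hoc method and any adjustment may properly sit in an analysis plan that is not shown. This stands, and it limits the consequence. It does not remove the mismatch: the article publishes an omnibus-first procedure that does not follow from its own primary objective, and it does not say which contrast the estimates are to serve.

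A reader might also infer more than the documents support:

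- *That a positive result says nothing about SSMP.* This is true only of the omnibus p-value. The pairwise step reports both SSMP contrasts for SPADI, NPRS and ROM.
- *That MWM beating sham would not support symptom modification.* The Background itself classes MWM as a symptom modification technique. Such a result would mislead only if it were presented as evidence for SSMP.
- *That MWM versus sham lies outside the study's aims.* The Abstract's Background gives a broader aim, comparing both approaches and sham. Only the primary objective is narrower.
- *That error control has failed.* A post-hoc step after an ANOVA is most naturally read as gated, and gating controls the error for three arms. The 12% applies only to ungated, unadjusted testing.
- *That PGIC will yield no SSMP contrast.* The Statistical analysis section names only the omnibus test, but the Discussion promises effect-size estimates for this outcome too.

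**Conclusion.** The point holds as a mismatch of moderate consequence between the primary objective and the SPADI analysis. An omnibus-first rule is a poor fit to a question about SSMP against two named comparators. At 12 per arm it can be significant in about 48% of trials when SSMP equals sham and MWM is better by 0.8 SD (21% to 68% for MWM effects of 0.5 to 1.0 SD). If used as a gate, it takes about 13 percentage points of power from SSMP versus sham (48% to 35%; 66% to 53% at the larger assumed effects).

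These figures rest on assumed effects, an assumed two-sided 0.05, normality, common variance, no dropout and no TENS covariate. The structural point does not depend on them.

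It would go too far to conclude that the pilot needs a confirmatory fixed sequence or an alpha split. No pass/fail decision is stated, and the primary objective does not rank its two comparators.

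**What to change.** In the Statistical analysis section, for SPADI, replace the omnibus-then-post-hoc rule with two pre-specified contrasts from one three-arm model that includes the covariates the plan uses: SSMP minus sham and SSMP minus MWM. Report each estimate with its 95% CI whatever the omnibus p-value. If a rank-based branch is kept, it should address the same two contrasts.

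Name the contrast that will inform the future trial's sample size. SSMP versus sham is the natural choice, because the Discussion gives the sham arm the task of separating specific from contextual effects. Label MWM versus sham, and all contrasts on NPRS, ROM and PGIC, as exploratory.

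This takes a few sentences and no further patients, visits or data. The article reports that recruitment is under way and that the final data go to a statistician at the end of the study, so the change should be made and dated before then. The small downside is that MWM versus sham loses its equal standing.

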### Intervention

Eligible participants will be randomly assigned to one of three groups: the SSMP (group A), MWM (group B), and Sham Intervention (group C). Each participant will undergo baseline assessment, and after assessment, they will be randomised and allocated into one of the three groups and will receive a four-phase designed specific rehabilitation procedures over an 8-week, followed by a follow-up session to assess improvements.

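### The primary SPADI comparison carries no baseline SPADI term and adjusts only for TENS use, which arises after randomisation

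*Protocol article*

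**What the plan says.** The Statistical analysis section names one method for the continuous outcomes (ROM, NPRS and SPADI): if the data are normal, "a One-Way ANOVA be used to assess differences across the three groups", with pairwise post-hoc tests after it. The alternative is also fixed: "For non-normal data, the Kruskal–Wallis test is appropriate, followed by Mann–Whitney tests to identify significant pairwise differences". One covariate is named: "TENS exposure will be included as a covariate in the primary outcome analyses". The same section promises a separate sensitivity analysis of the influence of TENS on NPRS and SPADI. It also says the main focus is on preliminary effect sizes with confidence intervals, to help size a later trial.

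SPADI is the primary outcome, measured at weeks 0, 4, 6 and 8 (Outcome measures). The baseline value precedes allocation: "Each participant will undergo baseline assessment, and after assessment, they will be randomised and allocated into one of the three groups" (Intervention). The text after Fig. 2 makes TENS available during the first two weeks when a participant's NPRS has not fallen since the previous session. The sample is 12 per arm, 36 in all, from a pilot rule of thumb (Sample size calculation).

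No baseline SPADI term is named. The section does not say which visit is compared, or whether follow-up or change scores are analysed.

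**The concern.** The baseline value of the outcome is usually its best available predictor. Here it is collected before randomisation, so treatment cannot affect it. Leaving it out of a trial with 12 per arm means that chance differences between arms at week 0 stay in the estimated effect, and variation between patients that baseline could explain stays in the error term. A pilot whose purpose is to estimate effects with intervals feels this directly, because its estimates feed the next trial's sample size.

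The covariate that is named does not fill the gap. TENS use depends on how pain moves after treatment starts, so it may itself be a consequence of the assigned arm, and adjusting for it can remove part of the effect being estimated. The section also does not fit together. An ANOVA with a covariate is no longer one-way, and the Kruskal–Wallis and Mann–Whitney tests cannot take a covariate at all.

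**Working it through.** **Inputs from the article.** n = 12 per arm, three arms, 3 × 12 = 36, which agrees with the stated total. No SD, target effect, power or dropout is given, so there is no power calculation to reproduce.

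**Assumptions.** 95% two-sided intervals; results in units of the SPADI SD, equal at baseline and follow-up; no missing data; baseline-to-follow-up correlation ρ between 0.3 and 0.7. The article gives no value of ρ.

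**Chance imbalance at baseline.** The difference between two arm means has standard deviation √(2/12) = 0.408 SD. For one given pair, P(|difference| > 0.5 SD) = 2 × [1 − Φ(0.5/0.408)] = 0.22. For at least one of the three pairs, 400,000 simulated sets of three means of 12 give 0.44. Given a gap of 0.5 SD, the follow-up contrast is expected to shift by ρ × 0.5: 0.15 SD at ρ = 0.3, 0.25 at 0.5 and 0.35 at 0.7.

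**Half-width of the 95% interval for one pairwise difference.**

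- Follow-up score, no baseline: t(0.975; 33) × √(2/12) = 2.035 × 0.408 = 0.83 SD.
- ANCOVA on baseline: t(0.975; 32) × √[(2/12)(1 − ρ²)(1 + 1/31)] = 0.845 × √(1 − ρ²). The factor 1 + 1/31 is the expected cost of estimating the slope.
- Change score, no covariate: t(0.975; 33) × √[(2/12) × 2(1 − ρ)].

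| ρ | No baseline | ANCOVA | ANCOVA narrower by | Change score |
|---|---|---|---|---|
| 0.3 | 0.83 | 0.81 | 3% | 0.98 |
| 0.5 | 0.83 | 0.73 | 12% | 0.83 |
| 0.6 | 0.83 | 0.68 | 19% | 0.74 |
| 0.7 | 0.83 | 0.60 | 27% | 0.64 |

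**In patients.** The squared ratio of unrounded half-widths is (0.8306/0.7317)² = 1.29, (0.8306/0.6759)² = 1.51 and (0.8306/0.6034)² = 1.90 at ρ = 0.5, 0.6 and 0.7. In variance terms that is about 29%, 51% and 90% more patients, or 15.5, 18.1 and 22.7 per arm. A larger trial would also gain degrees of freedom; allowing for that, the matching sizes are about 15.2, 17.7 and 21.9 per arm.

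**Break-even.** ANCOVA is wider only if 0.845 × √(1 − ρ²) > 0.831, that is, if ρ is below about 0.18.

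**The case against.** Four points can be made for the plan, and each limits the claim.

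- **The primary analysis is not wholly unadjusted.** A reader who stops at the one-way ANOVA might infer that it is, but TENS exposure is named as a covariate. What stands is that nothing measured before randomisation is adjusted for.
- **The comparison is not invalid, nor the least precise possible.** Under randomisation the follow-up contrast without a baseline term is unbiased on average, and its 0.83 SD half-width already reflects chance imbalance. The shift of 0.25 SD at ρ = 0.5 is therefore not an error on top of the wider interval. A change-score ANOVA would be wider still at ρ = 0.3 (0.98 SD) and equal at 0.5.
- **The article does not state the score or the visit.** It may intend change scores, which would use the baseline. ANCOVA is still narrower than change scores at every ρ in the table.
- **Unmodelled visits at weeks 4 and 6 do not by themselves widen a week-8 interval.** A reader might infer that they do. With complete data, a mixed model with unstructured covariance, arm-by-visit and baseline-by-visit terms gives essentially the same week-8 contrast as a week-8 ANCOVA. A gain needs missed visits, and the article gives no dropout rate. How missing visits are handled is also unstated and may be left to the full plan.

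It may also be said that a condensed article leaves covariates to an analysis plan that is not shown. That would answer mere silence. Here the article fixes the test and names a covariate, and the combination it fixes is a poor one.

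**Conclusion.** The point stands as a matter of baseline adjustment. The stated analysis has no baseline SPADI term, takes a post-randomisation variable as its only covariate, and offers a rank-test alternative that cannot accommodate that covariate. Over assumed correlations of 0.3 to 0.7, adding baseline narrows the pairwise 95% interval by 3% to 27%, from 0.83 SD to between 0.81 and 0.60 SD. It also removes the expected effect of a chance baseline gap, which exceeds 0.5 SD for a given pair with probability 22%.

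The size rests on ρ, which the documents do not give, and on equal SDs and complete data. At ρ = 0.3 the gain is slight; from about 0.5 it is worth having. This is a recommended improvement. It does not show that the planned comparison is biased on average, and it establishes no loss from leaving the intermediate visits out of the model.

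**What to change.** Make the primary analysis an ANCOVA of week-8 SPADI on arm and baseline SPADI, and state that week 8 is the visit compared. Use the same form for NPRS and ROM, each with its own baseline value. Report the SSMP–sham, SSMP–MWM and MWM–sham differences with 95% confidence intervals.

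Move the TENS-adjusted model into the sensitivity analysis that the article already promises, so that the primary estimate does not condition on a post-randomisation variable. Keep Kruskal–Wallis and Mann–Whitney for SPADI, NPRS and ROM as sensitivity analyses only.

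A mixed model over weeks 4, 6 and 8 with arm, visit, arm-by-visit, baseline and baseline-by-visit is an acceptable alternative. It helps mainly if visits are missed. It is also heavier for 36 people: nine arm-by-visit means, three baseline slopes and six covariance parameters.

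The ANCOVA costs one degree of freedom and a change of analysis wording, with no new data, visits or patients. The article lists the trial as recruiting and sends the data to the statistician only at the end, so by that account the change can be made before analysis begins.

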### Sample size calculation

As the study is a pilot study, the sample size will depend on the number of patients outflow to the Thumbay Hospital and rehabilitation hospital, Ajman. As for estimated we have decided 12 patients in each group as a thumb rule of pilot study [23].

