As the first study to investigate SSMP in frozen shoulder population, it aims to assess the feasibility, acceptability, and procedural fidelity of the symptom modification interventions, along with recruitment strategies using AC scale and patient adherence. It will provide preliminary effect size estimates for pain (NPRS), disability (SPADI), range of motion (ROM), and patient-reported outcomes (PGICS), informing sample size calculation for a future large-scale trial. The inclusion of sham mobilization will clarify whether observed improvements are due to specific therapeutic effects or nonspecific contextual factors critical for interpreting manual therapy outcomes in frozen shoulder rehabilitation.

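### An unspecified normality check at 12 per arm chooses between ANOVA and rank tests, and the rank branch as planned has no effect size, no confidence interval and no place for the required TENS covariate

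*Protocol article*

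**What the plan says.** The Statistical analysis section sets a two-way rule for the continuous outcomes, SPADI (primary), NPRS and ROM. The first branch reads: "if the data is normally distributed, a One-Way ANOVA be used to assess differences across the three groups, followed by post-hoc for pairwise comparisons". The second reads: "For non-normal data, the Kruskal–Wallis test is appropriate, followed by Mann–Whitney tests to identify significant pairwise differences". The section does not say how normality is judged, at what level, or whether raw values in each arm or model residuals are examined.

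Two further commitments stand in the same section. One concerns the primary outcome: "TENS exposure will be included as a covariate in the primary outcome analyses". The other concerns the purpose of the pilot: "the analysis will primarily focus on estimating preliminary effect sizes and confidence intervals". These are meant as input for planning a later full-scale study. The Discussion repeats that effect size estimates for pain, disability and range of motion will feed the next trial's sample size.

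Each arm has 12 patients, 36 in all (Abstract, Methods; Sample size calculation). Assessments after baseline are at weeks 4, 6 and 8.

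**The concern.** The outcome data choose the method, through a check that has little information at this sample size. The two branches also answer different questions. ANOVA with pairwise comparisons leads naturally to mean differences in scale points. Kruskal–Wallis and Mann–Whitney are planned only to find significant pairs, with no estimator or interval attached.

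If SPADI falls into the rank branch, following the text literally gives a p-value on ranks. It gives no between-group difference with an interval and no adjustment for TENS. If it falls there at one visit and not at another, the same outcome is reported on two scales. The next trial needs a difference and its precision in SPADI points, and could be left without a consistent set.

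**Working it through.** **Inputs from the protocol.** Three arms of 12 (3 × 12 = 36, which agrees with the stated total); three continuous outcomes; three visits after baseline; the two-branch rule; the TENS covariate; the estimation aim. The protocol gives no alpha, SD or effect size, so it has no figure of its own to reproduce beyond that sum.

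**Assumed.** Shapiro–Wilk at 5%, because no test is named. Two readings are shown: each arm checked separately with a switch if any arm rejects, and one check on the pooled residuals (n = 36). There were 3,000 simulated trials per distribution.

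**Step 1. Set the commitments against the branches.**

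| Commitment | One-way ANOVA as named | Kruskal–Wallis / Mann–Whitney as named |
|---|---|---|
| Effect size with CI | Follows directly as a mean difference | None specified |
| TENS as covariate | No place for it | No place for it |

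The covariate conflict therefore affects both branches. The missing estimate affects the rank branch only.

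**Step 2. How often the check rejects.**

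| True distribution | One arm of 12 | Any of three arms | Pooled residuals |
|---|---|---|---|
| Normal | 5% | 13% | 5% |
| Skewness 1.0 | 16% | 42% | 43% |
| Skewness 1.4 | 30% | 65% | 72% |

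The false-switch rate can be checked by formula. For three independent arms it is 1 − 0.95³ = 14.3%, against 13.1% simulated. At skewness 1.0 either reading sends the outcome to ranks in a little over four trials in ten, so chance largely settles the branch.

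**Step 3. Consistency across outcomes and visits, with truly normal data.**
- At least one of three outcomes switched, if independent: per arm 1 − 0.95⁹ = 37%; pooled 1 − 0.95³ = 14%.
- One outcome not on the same branch at all three visits, if visits are independent, is 1 − p³ − (1 − p)³. Per arm, p = 0.131 gives 1 − 0.002 − 0.656 = 34%. Pooled, p = 0.053 gives 1 − 0.000 − 0.849 = 15%.
- With an assumed between-visit correlation of 0.6, simulation of the per-arm reading gives about 35%, so independence is not driving the result.

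**Step 4. Error rates.** Across the distributions simulated (the three above plus exponential, uniform and t with 5 df), Type I error was 0.042 to 0.059 for the two-stage rule, 0.039 to 0.053 for ANOVA and 0.043 to 0.054 for Kruskal–Wallis. The switch does not inflate it.

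**Step 5. What a single analysis would deliver.** The 95% half-width for a pairwise mean difference is t × √(2/12) SD. With 22 df this is 2.074 × 0.408 = 0.85 SD; with 33 df it is 2.035 × 0.408 = 0.83 SD. Both are before any covariate adjustment. A Hodges–Lehmann interval from inverting Mann–Whitney at 12 v 12 has exact coverage 95.5% and a mean half-width of about 0.88 SD under normality, against 0.84 SD for the t interval in the same simulation.

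**The case against.** The strongest reply is that effect sizes and intervals are promised without restriction to one branch, so an analysis plan that is not shown could simply name an estimator for the rank branch. A reader might infer that rank tests cannot give an interval. Step 5 shows that this is wrong: a Hodges–Lehmann shift in SPADI points with near-nominal coverage is available. What stands is narrower. The article states what the rank tests are for, and that purpose is significance. A shift estimate would also still not be the mean difference reported elsewhere, nor one adjusted for TENS. An added estimator would not remove the switch.

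The size of the problem also depends on the assumed check. Pooled residuals cut false switching from 13% to 5% and raise detection of skewness 1.0 from 16% in a single arm to 43%. That is why both readings are given.

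Two stronger readings are not supported:
- That pairwise contrasts are withheld unless the omnibus test is significant, with a loss of power. The text says only that one follows the other. The apparent loss for SSMP–sham (66% ungated against 53% gated, for a 1 SD difference with MWM midway) compares unequal error control: three unadjusted contrasts carry 11.9% familywise error against 4.9% gated, and Tukey-adjusted power is 51%.
- That integer scoring pushes outcomes into the rank branch generally. It can for NPRS-like scores (29% to 57% of trials per arm and 8% to 32% pooled, part of it a floor effect). A SPADI-like 0–100 score rejected in 13%, the same as unrounded normal data.

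**Conclusion.** The point holds as an internal conflict in the stated plan. Followed literally, the plan can leave the primary outcome without the adjusted estimate and interval that it names as its main product, and a chance-driven check decides when. Because the conflict lies between sentences of one section, it is more than detail left for later.

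The harm lies in inconsistent or absent estimates; the test results themselves remain valid. The figures rest on Shapiro–Wilk at 5% and on the simulated distributions, none of which the protocol specifies. The conflict between the rank branch, the covariate and the estimation aim rests on the text alone. The change should be made, and the article gives the study status as recruiting, so it can precede the final analysis.

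**What to change.** Delete the conditional choice between ANOVA and rank tests for SPADI, NPRS and ROM. Pre-specify one baseline-adjusted linear model for these outcomes. Report the SSMP–sham, SSMP–MWM and MWM–sham mean differences with 95% CIs at each visit, whatever a normality or omnibus test shows. Such a model has room for the TENS term that the section requires; whether a measure recorded after randomisation should be adjusted for is a separate question.

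Use a bootstrap interval, or a rank analysis reporting the Hodges–Lehmann shift with its CI, as a sensitivity analysis only. Keep Kruskal–Wallis for the ordinal PGIC.

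The cost is a change of wording and one sensitivity run on data already being collected. The small downside is that non-normality is then handled by the sensitivity analysis and no longer by changing the main method.

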**Fig. 2 Fig2:**
[figure not shown]
Exercises of functional program

Transcutaneous Electrical Nerve Stimulation (TENS) will be permitted as a standardized rescue analgesic intervention during the first two weeks only if a participant reported an NPRS score equal to or higher than the previous session. The TENS parameters (frequency, pulse duration, intensity, and treatment duration) will be standardized across all groups to ensure uniform exposure. The frequency of TENS usage shall be documented and later incorporated into statistical analysis as a covariate to minimize any confounding effects. TENS The frequency of TENS application will be recorded across all groups.

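### Rescue TENS, triggered after randomisation by the participant's own NPRS, is fixed as a covariate in the primary SPADI analysis, so the adjusted contrast does not estimate the effect of randomised assignment

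*Protocol article*

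**What the plan says.** All references are to the protocol article.

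- **Order of events** (Intervention): "Each participant will undergo baseline assessment, and after assessment, they will be randomised and allocated into one of the three groups". Treatment, and any TENS, follows.
- **Trigger** (rescue paragraph after Fig. 2, under Phase IV—Functional programme): TENS is permitted "during the first two weeks only if a participant reported an NPRS score equal to or higher than the previous session".
- **Planned use in the analysis** (same paragraph): "The frequency of TENS usage shall be documented and later incorporated into statistical analysis as a covariate to minimize any confounding effects".
- **Primary model** (Statistical analysis): "TENS exposure will be included as a covariate in the primary outcome analyses". No condition is attached. A separate sensitivity analysis of the influence of TENS on NPRS and SPADI is also announced.
- **Named tests** (Statistical analysis): "a One-Way ANOVA be used to assess differences across the three groups, followed by post-hoc for pairwise comparisons", with Kruskal–Wallis and then Mann–Whitney tests for non-normal data.
- **Outcomes** (Outcome measures): SPADI is the primary outcome; NPRS is secondary.
- **Purpose** (Statistical analysis and Discussion): the focus is on preliminary effect sizes and confidence intervals, from which a definitive trial will be designed and sized.

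**The concern.** Randomisation already deals with confounding between arm and outcome. A variable that arises afterwards, in response to how the participant is doing, cannot be a confounder of that comparison. Here the trigger is the participant's own pain score failing to fall. That score is a secondary efficacy outcome, and it is closely related to the primary outcome, which is itself an index of pain and disability.

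Holding TENS count fixed means comparing participants from different arms who had a similarly poor early pain course. Part of what the treatment may have achieved is then held constant. TENS count also shares unmeasured causes with SPADI, such as individual responsiveness, so the adjusted groups are no longer the groups that randomisation made comparable.

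At stake is the pilot's main quantitative product. If the SSMP–sham and MWM–sham contrasts on SPADI are taken from this model, the definitive trial will be planned on a quantity other than the effect of assignment.

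**Working it through.** **The plan's own figure.** The only figure is the sample size, 3 × 12 = 36, a rule of thumb. It agrees, and it does not depend on the analysis model. The documents give no TENS use, NPRS course or SPADI standard deviation, so the bias can be described but not measured.

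**Step 1: the algebra.** Let γ be the within-arm slope of SPADI on TENS count, and ΔT the mean TENS count in the active arm minus that in sham. In a linear model

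adjusted effect = total effect − γ × ΔT.

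Lower SPADI is better, so a benefit is negative. If the active arm uses one fewer application (ΔT = −1):

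- γ = +2: the adjusted effect is 2 points nearer zero.
- γ = +4: 4 points nearer zero.
- γ = 0, or ΔT = 0: no shift.
- γ = −2: 2 points further from zero.

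γ combines two opposing things: TENS marks a poor early course (positive), and TENS may itself help (negative).

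**Step 2: an illustration.** Three sessions a week (Abstract, Methods) give 6 sessions in the TENS window and 5 session-to-session comparisons, unless a pre-treatment NPRS counts as a session.

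Everything else is assumed:

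- 200,000 participants per arm, active versus sham.
- Baseline NPRS mean 7, SD 1.2, rounded to whole numbers.
- Mean change per session −0.15 in sham and a further −0.25 in active; between-person slope SD 0.25.
- TENS counted each time NPRS is equal to or above the previous value.
- Week-8 SPADI = 60 + 40 × slope + (TENS effect × count) + residual with SD 12.

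| Session noise SD | SPADI effect per TENS use | Mean TENS, sham / active | γ | Total effect | Adjusted | Adjusted ÷ total |
|---|---|---|---|---|---|---|
| 0.5 | 0 | 3.35 / 2.75 | 6.93 | −9.97 | −5.80 | 58% |
| 0.5 | −3 | 3.35 / 2.75 | 3.93 | −8.22 | −5.88 | 72% |
| 1.0 | 0 | 2.99 / 2.65 | 5.04 | −9.97 | −8.24 | 83% |
| 1.0 | −3 | 2.99 / 2.64 | 2.06 | −9.01 | −8.29 | 92% |

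The first row agrees with the algebra: −9.97 − 6.93 × (2.75 − 3.35) = −9.97 + 4.16 = −5.81, against −5.80 before rounding. A larger assumed slope difference (−0.40) gave nearly the same percentages.

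**Step 3: does the direction hold under other inputs?** Not always. These runs used 30 SPADI points per unit of slope:

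- Slope SD 0.40, noise 0.5, TENS inert: adjusted effect about 60% smaller.
- Slope SD 0.15, noise 0.5 to 0.8, TENS worth 3 points per use: 4% to 9% larger.
- Slope SD 0.05, TENS worth 1 to 3 points per use: roughly 5% to 30% larger.
- Early slope unrelated to week-8 SPADI within arm, TENS inert: no change.

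**Step 4: the named tests.** One-way ANOVA, Kruskal–Wallis and Mann–Whitney have no place for a covariate. The same section asks for one in the primary analysis, so the section cannot be carried out as written.

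**The case against.** **A sensitivity analysis on TENS is already planned.** True, but the covariate sentence puts TENS in the primary model, and no comparison without TENS is designated primary. The sensitivity analysis does not undo that.

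**The named one-way ANOVA is itself free of TENS, and adding a covariate ordinarily just means ANCOVA.** This is fair, and a fuller analysis plan may say so. It makes the conflict over tests a lesser point for the parametric route, although the rank-based fallback stays unreconciled. It does not help the main point, because ANCOVA on TENS is the problem.

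**The sponsor may want the effect had TENS not been used.** The documents state no such aim. A TENS count as covariate would not deliver it either, since the count also marks poor responders.

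**It is a small pilot.** With 12 per arm and an assumed SPADI SD of 15 to 25, the standard error of a pairwise difference is SD × √(2/12), about 6 to 10 points. The largest shift in the table, 4.2 points, is below one standard error. That limits the practical weight of the point but does not excuse a systematic error in the quantity the pilot exists to supply.

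**Stronger readings that a reader might infer, and which the documents do not support:**

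- *Adjustment necessarily removes part of the treatment effect.* The shift is zero if mean TENS use is equal across arms or unrelated to SPADI within arms, and it can reverse if TENS helps enough.
- *The covariate is fixed for NPRS as well.* The Statistical analysis section fixes it for the primary outcome, which is SPADI alone. The wider wording of the rescue paragraph only leaves the same adjustment of NPRS possible.
- *Almost everyone will receive TENS.* An unchanged NPRS meets the trigger, so eligibility may be common, but TENS is permitted rather than required. The simulations count every trigger as a use.

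**Conclusion.** The point stands as a wrong stated choice, not as missing detail. TENS use follows randomisation and depends on the participant's own early NPRS, so calling it a confounder is mistaken. The TENS-adjusted SPADI contrast does not estimate the effect of randomised assignment.

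Attenuation is the most likely direction, provided effective treatment lowers early NPRS and TENS does little itself. Neither direction nor size can be determined from the documents. The percentages above show only that the shift can matter; they are not forecasts for this trial. The mismatch between the covariate and the named tests is a secondary inconsistency to be reconciled at the same time. Nothing here bears on the rescue rule itself.

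**What to change.** By dated amendment, before outcome data are analysed:

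1. Delete the TENS covariate sentence in Statistical analysis and the covariate clause in the rescue paragraph. Keep the recording of TENS use.
2. State that the primary SPADI comparison, and likewise NPRS, is by arm as randomised regardless of TENS use. With the TENS covariate gone, the conflict with the named tests goes too.
3. Report TENS use by arm descriptively.
4. Keep any TENS-adjusted model only within the sensitivity analysis already planned, labelled exploratory and not an estimate of the randomised treatment effect.

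The cost is the amendment and its documentation. No new data are needed, since TENS use is already recorded, and the sample size stays at 36. The trial began in January 2025 and the article lists it as recruiting, with completion due by July 2026, so the amendment should be dated and its timing relative to the analysis stated. No change to the rescue rule is proposed.
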